## Abstract

**Background:**

Surgery is still the standard treatment for breast lesions such as *in situ* ductal carcinoma (DCIS); however, its survival benefit is minimal, particularly for low-grade DCIS. Surgical complications and related depression status can adversely affect patients’ quality of life. Approximately 25% of breast cancer (BC) cases are *in situ* forms, with DCIS making up 90% of these. Low and intermediate-grade DCIS often grow slowly and do not always progress clinically significant diseases. Identifying non-invasive lesions could help prevent overtreatment. In this context, new diagnostic tools like vacuum-assisted excision (VAE) could enhance the management of these conditions.

**Methods:**

The prospective VACIS study explores the role of VAE in ensuring the absence of pathology at subsequent surgery and reducing the diagnostic underestimation of breast biopsies for microcalcifications. Patients with suspicious breast microcalcifications up to 15 mm, who are candidates for stereotactic biopsy, will be enrolled and randomised into two groups. The control group will complete the biopsy with typical sampling, aiming to collect some microcalcifications from the target, while the experimental group will focus on the complete removal of the biopsy target (confirmed by mammography on the biopsy table), followed by a second sequence of cleaning samples. Radiograms will confirm lesion removal. Pathologic outcomes at surgery will be compared between the groups, and the percentage of underestimation will be assessed. The sample size is calculated to be 70 patients per group, using statistical tests and multivariate logistic models to detect a significant difference in the absence of pathology. Data collected will include patient age, lesion characteristics, and details of the biopsy, pathology and surgery.

**Discussion:**

Current surgical treatments for low-and sometimes intermediate-grade DCIS offer limited survival benefits and may hurt patients’ quality of life due to surgery-related complications and associated depression. These lesions often grow slowly and might not become clinically significant, suggesting a need to avoid overtreatment. Improved diagnostics procedures, such as VAE, could help distinguish non-invasive from potentially invasive lesions, reduce biopsy underestimation, enable personalised management and optimise treatment strategies. This study hypothesises that VAE could be a viable alternative to surgery, capable of removing pathology during the biopsy procedure.

**Clinical trial registration:**

Clinicaltrials.gov, identifier NCT05932758.

## Introduction

The advent of breast mammography screening has significantly increased the diagnosis of *in situ* breast lesions (1). Approximately 25% of all BC cases are *in situ*, meaning the cancerous growth is confined to the duct or lobule and is generally clinically occult with minimal potential for spread. Notably, DCIS accounts for 90% of *in situ* BCs (2). Managing these lesions represents a significant economic and health challenge.

Surgery remains the standard for breast lesions like DCIS (3). Over 98% of patients diagnosed with DCIS undergo surgical procedures, often in combination with radiotherapy (RT). However, most cases rarely progress to invasive BC, with a mortality rate of only 4% (4). The risk of progression and aggressiveness is associated with disease grade, with high-grade tumours linked to a poorer prognosis (4). Research suggests that greater aggressiveness is also related to multifocality and abnormal branching and lobularization, known as neoductgenesis (4). Identifying these patterns through imaging and histology may help recognise inherent aggressiveness and tailor treatment accordingly. Thus, aggressive treatment for DCIS, especially in patients with additional health issues, might constitute overtreatment (5). The survival benefit of surgical resection in these patients is low, especially for low-grade DCIS, where surgical comorbidities and prior depression are linked to a poorer quality of life (6). Low-grade and sometimes intermediate-grade DCIS typically exhibit slow growth and often do not progress to clinically significant disease (6). Therefore, distinguishing harmless lesions from potentially invasive ones can help avoid overtreatment in many patients. Nonetheless, the public health costs of surgery and prolonged follow-up remain comparable.

Recent studies have focused on identifying less aggressive forms of *in situ* lesions to enable the de-escalation of conventional treatments (4). A growing interest is in personalised medicine tailored to the patient’s specific pathology. Four international prospective study protocols (LORIS, COMET, LORD, and LORETTA) are currently evaluating non-invasive treatment methods for DCIS (7), primarily aiming to assess the effectiveness and safety of active surveillance compared to surgery-based approaches for low-risk DCIS patients.

Our study protocol (VACIS protocol) aims to identify a population of patients for whom non-surgical management can be proposed more safely. Enhancing the effectiveness of active surveillance involves reducing the upgrade rate where DCIS confirmed by presurgical biopsy is later reclassified as invasive carcinoma in surgical specimens (8). Data on the underestimation rate of DCIS diagnoses is contentious. A significant meta-analysis by Brennan et al. (8) found that up to 26% of patients with biopsy-confirmed DCIS had synchronous invasive carcinoma in surgical specimens. Consequently, efforts should focus on identifying factors that lead to biopsy underestimation (infiltrating tumours diagnosed as DCIS) and identifying patients at risk of developing the invasive disease during follow-up. Current evidence suggests that new diagnostic and interventional techniques, such as VAE, can significantly reduce the rate of diagnostic underestimation and help identify patients with distinct disease progression, allowing for personalised management.

VAE involves the removal of at least 4 grams of breast tissue using a vacuum-assisted biopsy (VABB). In our study protocol, we have standardized the procedures by dividing them into an initial sequence of extractions that remove the lesion and a second sequence of extractions, referred to as “cleaning,” akin to a surgical procedure. The primary aim of this study protocol is to investigate the relationship between the role of VAE and the lack of pathology *in situ* at subsequent surgery. Could VAE substitute surgery in some patients with low-grade DCIS categories? Since most *in situ* forms are microcalcifications, the study protocol is focused exclusively on stereotactic biopsies. The secondary aim is to evaluate the role of VAE in reducing the diagnostic underestimation of the breast biopsy with a histological result of DCIS.

### Ethics and consent

The study protocol has been evaluated and authorised by the European Institute of Oncology ethical (number of approval IEO 1856) committee. Participants will sign written informed consent, and researchers will adhere to institutional data collection and management guidelines.

## Methods and analysis

The study is a two-arm trial involving 300 patients (*n* = 150 in the VAE group and *n* = 150 in the non-VAE group) over 36 months. Participants are randomly assigned to either the VAE (intervention) or standard-of-care (control) group.

In the control group, biopsies will follow the typical sampling procedure aimed only at collecting some microcalcifications from the target. In the VAE group, the focus will be on the complete removal of the biopsy target, confirmed by mammography on the biopsy table, followed by a second sequence of cleaning samples. Radiograms will confirm lesion removal for the intervention group. Pathology analysis will report separately each sample. Pathological outcomes at surgery will be compared between the two groups. To adhere to the protocol, it is necessary to have a digital stereotactic biopsy guidance system (with a dedicated patient table).

A statistical comparison will be performed to evaluate the differences between the VAE and Standard-of-care groups.

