All patients with low and intermediate-grade DCIS histological findings will be included in the study and are expected to be evenly distributed between the VAE and control groups. These patients will undergo surgery, and we will compare the percentage of patients with no pathology (including *in situ*) at the surgery between the two groups to determine if VAE can effectively remove small lesions and potentially serve as an alternative to surgery. The surgical specimens will be radiographed to verify the presence of the post-biopsy clip in the surgical sample. We will also compare the rate of biopsy underestimation of invasive carcinoma between the groups. The surgical tissue sections will be documented to ensure consistency between the two groups.

Our goal is to enroll at least 300 patients in this study. We focus on stereotactic VABB because *in situ* neoplasms predominantly present as microcalcifications, and complete macroscopic removal of the lesion can be more easily verified with mammography rather than ultrasound. The study design is summarized in Figure 1.

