### Statistical analysis

The primary endpoint is to compare the percentage of patients with no detectable pathology at surgery between the group undergoing standard treatment (macroscopical removal of the lesion) and the group undergoing VAE (VAE group). Based on the assumption that macroscopical removal without VAE will result in approximately 20% of patients having no pathology at the subsequent surgery, a sample size of 70 patients per arm is calculated to achieve 90% power to detect a 16% difference between the two treatment groups.

This calculation is based on an inequality test for two independent proportions, assuming a 0.2 proportion under the null hypothesis (standard treatment group) and a 0.04 proportion under the alternative hypothesis (VAE group). The test statistic will be the two-sided Z test with pooled variance, using a significance level 0.05.

Continuous variables will be summarized with the median and interquartile range for each treatment arm, while categorical variables will be presented as frequency and percentage. Differences between the two groups will be evaluated using the Wilcoxon rank-sum test for continuous variables and the chi-square test for categorical variables. Multivariate logistic regression models will be used to assess the association between the treatment group and the absence of pathology at surgery, adjusting for key clinical variables and potential confounders. The results will be quantified in terms of odds ratios (Ors), with statistical significance evaluated using *p*-values and a significance threshold set of 0.05.

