Our study aims to identify patients for whom active surveillance can be safely recommended, thereby increasing the enrollment in non-operative management of DCIS. The role of VAE as a potential alternative to surgery has already been successfully investigated for benign lesions and, in preliminary stages, for high-risk lesions (19). We believe that its role in managing *in situ* lesions could be equally promising.

One of the study’s strengths is the integration of VAE on the same day and during the same session as the conventional biopsy procedure. This method offers significant time and economic savings and reduces psychological stress for the patient. However, this protocol will likely result in performing VAE in many patients who do not have *in situ* pathology, as the histological outcome is not known at the time of the biopsy. We believe the risks associated with VAE are minimal and not significantly higher than those of the standard stereotactic procedure. Anyway, the percentage of hematomas and peri-biopsy complications will be recorded and compared between the two groups.

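### The protocol gives both 300 patients and 70 per arm without saying how they relate, so the evaluable number behind the stated power is not fixed

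*Protocol article*

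**What the plan says.** Two sizes appear in the protocol article.

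- **300 in total.** Methods and analysis: "The study is a two-arm trial involving 300 patients", split as 150 in the VAE group and "150 in the non-VAE group) over 36 months". Study design: "Our goal is to enroll at least 300 patients in this study".
- **70 per arm, 140 in total.** Abstract, Methods: "The sample size is calculated to be 70 patients per group". Statistical analysis: "a sample size of 70 patients per arm is calculated to achieve 90% power to detect a 16% difference between the two treatment groups". The inputs are proportions of 0.20 (standard) and 0.04 (VAE), a two-sided Z test with pooled variance, and a significance level of 0.05.

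Two populations also appear. Study design enrols and randomises 1:1 on a mammographic lesion under 15 mm. The Discussion confirms that histology is unknown at that point and expects that "this protocol will likely result in performing VAE in many patients who do not have" in situ disease. Study design and the eligibility lists then keep only patients whose biopsy shows low- or intermediate-grade DCIS and who have surgery. In the VAE arm only, they also remove patients in whom a haematoma stops the second sampling sequence. The primary endpoint is observed at surgery.

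**The concern.** Power depends on how many patients reach surgery with the qualifying histology, and that number is settled only after randomisation. A plan of this kind needs a randomised number, an evaluable number and the fraction linking them. The article gives two numbers, labels neither explicitly and states no fraction.

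If the 300 are randomised patients, the evaluable number could fall well short of 70 per arm. This would emerge only once histology had accumulated, and patients without DCIS would have had the experimental procedure without contributing to the primary comparison. If the 300 are DCIS patients, the sample-size calculation does not describe the trial, and the recruitment load is larger than any figure given.

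**Working it through.** **Inputs.** From Statistical analysis: p1 = 0.20, p2 = 0.04, difference d = 0.16, two-sided alpha 0.05 (z = 1.960), power 90% (z = 1.2816), pooled variance. From Methods and analysis: 300 in total, 1:1. The yield y is the share of randomised patients who have qualifying DCIS, reach surgery and are not otherwise excluded. It is not in the documents, so the values of y below are assumptions.

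**Step 1: the plan's own figure.** Mean proportion = (0.20 + 0.04)/2 = 0.12.

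- A = √(2 × 0.12 × 0.88) = √0.2112 = 0.4596
- B = √(0.20 × 0.80 + 0.04 × 0.96) = √0.1984 = 0.4454
- n per arm = (1.960·A + 1.2816·B)² / d² = (0.9007 + 0.5708)² / 0.0256 = 84.6, so **85**

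The stated 70 is not reproduced. Power at n per arm is Φ[(d√n − 1.960·A)/B]. At n = 70 this is Φ[(1.3387 − 0.9007)/0.4454] = Φ(0.983) = **83.7%**, or 87.0% by exact binomial calculation of the same test. Other two-sided methods for 90% give 77 (arcsine), 82 (unpooled) and 97 (continuity-corrected). By exact calculation, 80 per arm gives 91.0%. Only a one-sided test comes close to 70: it needs 69, and 70 gives 90.5%.

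**Step 2: yield needed if 300 are randomised.** y = 2n/300.

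- For 70 per arm: 140/300 = **46.7%**
- For 90% power with the stated test: 170/300 = **56.7%**
- With the other two-sided methods: 154/300 = 51.3% (arcsine), 164/300 = 54.7% (unpooled), 194/300 = 64.7% (continuity-corrected)

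**Step 3: power from 300 randomised at assumed yields.** Evaluable per arm = 150y, and power is from the Step 1 formula.

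| Assumed yield | Evaluable per arm | Power, 0.20 vs 0.04 | Randomised for 140 evaluable (140/y) |
|---|---|---|---|
| 20% | 30 | 48% | 700 |
| 30% | 45 | 65% | 467 |
| 40% | 60 | 78% | 350 |
| 50% | 75 | 86% | 280 |

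Exact binomial power at these sizes is 53%, 71%, 81% and 89%, so the pattern does not depend on the approximation. The table assumes equal arms. The haematoma exclusion, for which no rate is given, would lower the VAE arm further.

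**Step 4: if all 300 are evaluable.** At n = 150, power = Φ[(1.9596 − 0.9007)/0.4454] = Φ(2.377) = **99.1%**. The number to randomise is then 300/y, for example 1,500 at 20% or 600 at 50%, and none is stated.

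**The case against.** The strongest defence is that the two sizes do not conflict. The endpoint exists only at surgery, so the 70 must be patients who reach it. Study design uses the same verb, enrol, for the 300 and for the group randomised before biopsy. On that reading 300 are randomised in order to obtain at least 140 evaluable patients, and only the linking assumption is absent. A condensed article may leave such a step to the full protocol.

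Much of this stands. A reader might infer a flat contradiction, or that neither number belongs to any population. The wording does not support either inference, because it leans towards 300 randomised and 70 evaluable. A missing yield would also not be a finding by itself. What remains is that the article prints two totals, calls 300 the trial size in one section and calculates 140 in another. It also lists DCIS after biopsy as an inclusion criterion, which keeps the other reading of the 300 open.

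Three further inferences should be resisted.

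- **That a 47% yield secures the stated power.** It secures only 70 per arm, which gives 83.7% under the stated test.
- **That the text tells the team to stop at 300 biopsied patients.** Study design sets 300 as a minimum, and no stopping number is stated.
- **That the trial is shown to be underpowered.** The Discussion expects many patients without in situ disease, but that is compatible with a yield near one half. At 50% the trial would have 75 per arm, more than the 70 calculated.

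**Conclusion.** The point holds as an unreconciled sample size. The evaluable number that determines power is not fixed by the document, and the two readings of the 300 lead to very different trials.

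- **300 randomised (the more natural reading):** the plan relies on an unstated yield of 46.7% for 70 per arm, or 56.7% for 90% power with the stated test. Across assumed yields of 20% to 50%, power runs from 48% to 86%.
- **300 evaluable:** there is no shortfall on the plan's inputs (99%), but the 70-per-arm calculation is not the trial's size and the randomisation target is missing.

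The existence of two unlinked totals is certain. The size of any power loss is conditional on the first reading and on a yield that the documents do not supply. All power figures take the plan's 0.20 and 0.04 as given. Whether those proportions run in the right direction for an endpoint of no pathology at surgery is a separate question and is not counted here.

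**What to change.** State one evaluable target per arm, defined as low- or intermediate-grade DCIS on biopsy followed by surgery, and one number to randomise. Link them by an explicit yield: randomised = evaluable / yield. Take the yield from the centre's own stereotactic biopsy records for lesions of this size, and allow for patients who do not reach surgery and for the haematoma exclusion. Use the same pair of numbers in the Abstract, Methods and analysis, Study design and Statistical analysis. Recalculate the evaluable target with the test actually named, since 70 per arm does not give 90% with it.

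Define the end of recruitment by the evaluable count. If 300 randomised cannot change, keep it and restate the power at the evaluable number it implies.

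The cost is some rewording and one look at existing records. The stated power may fall. If the power is restated, no extra patients are needed. If the evaluable target is kept and the yield is below the level required, recruitment must be larger or longer than the 36 months now given.

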### Study design

All patients with suspicious breast lesions (BI-RADS ≥3) who are candidates for stereotactic VABB and whose lesions present as microcalcifications (the most common form of low and intermediate-grade DCIS) will be prospectively selected. The radiologists involved in the procedure are all dedicated to breast imaging and have at least 5 years of work experience. Patients with a mammographic lesion measuring less than 15 mm in diameter will be enrolled and randomly assigned into two groups on a 1:1 basis. The randomization data will be securely stored on a password-protected computer at the European Institute of Oncology, accessible only to researchers involved in the study.

In the control group, biopsies will focus solely on sampling a few microcalcifications (fewer than 12 samples) and may not necessarily use an 8G needle. In the VAE group, the lesion will be macroscopically removed using an initial sequence of at least eight samples with an 8G needle, followed by a cleaning sequence of at least four samples. This group will undergo an excisional biopsy (VAE) according to United Kingdom guidelines, which define VAE as a collection of at least 4 grams of tissue with an 8G needle. The VAE will be performed during the same biopsy session without recalling the patient later. Both groups will receive post-procedure mammograms and specimen radiograms. The specimen radiogram is used to separate the specimens with microcalcifications from those without, to assist the pathologist, and to verify that the biopsy procedure has indeed sampled the target microcalcifications. We also have the ability to obtain mammographic images while the patient is still on the biopsy table. For the interventional group, if residual microcalcifications are present, the sampling will continue until they are completely removed. For the control group, the goal is not the complete removal of the target but rather the correct diagnostic procedure, so even if residual microcalcifications remain after the biopsy, the procedure will be concluded.

All patients with low and intermediate-grade DCIS histological findings will be included in the study and are expected to be evenly distributed between the VAE and control groups. These patients will undergo surgery, and we will compare the percentage of patients with no pathology (including *in situ*) at the surgery between the two groups to determine if VAE can effectively remove small lesions and potentially serve as an alternative to surgery. The surgical specimens will be radiographed to verify the presence of the post-biopsy clip in the surgical sample. We will also compare the rate of biopsy underestimation of invasive carcinoma between the groups. The surgical tissue sections will be documented to ensure consistency between the two groups.

Our goal is to enroll at least 300 patients in this study. We focus on stereotactic VABB because *in situ* neoplasms predominantly present as microcalcifications, and complete macroscopic removal of the lesion can be more easily verified with mammography rather than ultrasound. The study design is summarized in Figure 1.

**Figure 1 fig1:**
[figure not shown]
Study design.

#### Inclusion criteria

Patients with suspicious breast lesions (BI-RADS ≥3) presenting as microcalcifications.Patients capable of and willing to comply with the specific informed consent form.Patients undergoing stereotactic VABB.Patients with low to intermediate-grade DCIS following biopsy.Patients scheduled for surgery.

#### Exclusion criteria

Patients undergoing other types of biopsies (not stereotactic).Patients whose lesions are not in the form of microcalcifications.Patients who refuse to sign the specific informed consent.Patients whose histological biopsy result is not low/intermediate-grade DCIS.Patients with multifocal and/or multicentric lesions.Patients who will not undergo surgery.For the VAE group only: patients in whom haematoma prevents the continuation of the second sequence of biopsies.

The data to be recorded during the biopsy procedure are listed in Table 1.

**Table 1 tab1:** Data recorded during the biopsy procedure.

Characteristics	
**Age (years)**	**Needle (Gouge)**
**Menopausal status**	7G
Pre-	8G
Post-	10G
**Lesion side**	11G
Right	**Samples (n)**
Left	**Lesion excision**
**Lesion site**	Minimal
Upper-outer	Partial
Lower-outer	Complete
Upper-inner	**Clip**
Lower-inner	Yes
Retroareolar	No
Inner-equatorial	**Clip placement**
Outer-equatorial	On-site
Upper-hemitelic	Dislocated
Lower-hemitelic	**Clip dislocation (from the sampling site)**
**Lesion size (mm)**	Distance (mm)
**Lesion type**	Sector (upper, lower, outer, inner)
Microcalcifications	**VAE**
Architectural distortion	Yes
Lump	No
Asymmetry	**Complications**
**VABB type**	Yes (additional notes)
Stereotactic	No
Tomographic	**Histological findings**
Ultrasound	

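### Patients are randomised before biopsy but analysed only if that arm-dependent biopsy shows low/intermediate-grade DCIS, so the primary contrast can favour VAE without better removal

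*Protocol article*

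**What the plan says.** Under Study design, patients with a lesion below 15 mm on mammography "will be enrolled and randomly assigned into two groups on a 1:1 basis". The arm is the biopsy technique. Control takes fewer than 12 samples, not necessarily with an 8G needle. VAE takes at least eight samples with an 8G needle, then at least four cleaning samples, and sampling goes on until no calcification remains. "The VAE will be performed during the same biopsy session without recalling the patient later", and the Discussion accepts that "the histological outcome is not known at the time of the biopsy".

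Eligibility is completed afterwards. The Inclusion criteria require "Patients with low to intermediate-grade DCIS following biopsy". The Exclusion criteria remove "Patients whose histological biopsy result is not low/intermediate-grade DCIS", "Patients who will not undergo surgery" and, in one arm, "For the VAE group only: patients in whom haematoma prevents the continuation of the second sequence of biopsies".

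Study design says that the DCIS patients "are expected to be evenly distributed between the VAE and control groups" and compares the arms among those patients on the percentage with no pathology at surgery. The Statistical analysis section makes that percentage the primary endpoint. The Introduction gives as secondary aim that VAE should reduce underestimation, meaning invasive tumours labelled DCIS at biopsy.

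**The concern.** The biopsy result is an outcome of the randomised procedure, and the plan uses it to decide who is analysed. If VAE works as the secondary aim supposes, some lesions that limited sampling would call DCIS are recognised as invasive in the VAE arm, and those patients are dropped. The same kind of patient in the control arm is kept and, by the definition of underestimation, has pathology at surgery. The VAE denominator loses cases that could not have been clear; the control denominator does not.

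The haematoma rule is a second filter, and it applies to one arm by its own wording. It removes VAE patients in whom the assigned procedure could not be completed, with no control equivalent.

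At stake is the interpretation of the primary result. The article asks whether VAE could replace surgery in some patients, and a difference produced by reclassification could be read as lesions removed. Equal numbers of DCIS patients per arm would not settle this, because the case mix would still differ.

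**Working it through.** **The plan's own figure.** The Statistical analysis section gives 70 per arm for 90% power, 0.20 against 0.04, two-sided pooled Z test at 0.05. The formula gives n = [1.96·√(2·0.12·0.88) + 1.2816·√(0.20·0.80 + 0.04·0.96)]² / 0.16² = 84.6, so 85 per arm. A one-sided test gives 69. This mismatch is a separate matter and does not enter the working below. The plan gives no figure for how biopsy results will split between the arms.

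**Inputs.**
- Control clearance at surgery 0.20 (Statistical analysis).
- Hidden invasion u among DCIS diagnosed by limited sampling: at most 0.26 (meta-analysis cited in the Introduction). The value 0.10 is an assumption.
- Share r of that hidden invasion found by VAE at biopsy: 0.5 or 1, an assumption.
- VAE clears no additional lesion: a deliberate assumption, to isolate the selection effect.

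**Formula.** Take 100 patients per arm whose lesions limited sampling would call low/intermediate-grade DCIS. In control all 100 are analysed and 20 are clear. In the VAE arm 100·u·r are reclassified and leave; none of them would have been clear, so 20 clear patients remain among 100·(1 − u·r). The apparent VAE rate is 0.20 / (1 − u·r).

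The last two columns give the exact binomial rejection rate of the two-sided pooled Z test, which is 5.1% and 5.0% when both arms are truly at 20%.

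| u | r | VAE rate | Spurious gain | Rejection, 70 per arm | Rejection, 150 per arm |
|---|---|---|---|---|---|
| 0.10 | 0.5 | 0.20/0.95 = 21.1% | 1.1 points | 5.4% | 5.6% |
| 0.10 | 1 | 0.20/0.90 = 22.2% | 2.2 points | 6.3% | 7.6% |
| 0.26 | 0.5 | 0.20/0.87 = 23.0% | 3.0 points | 7.3% | 9.7% |
| 0.26 | 1 | 0.20/0.74 = 27.0% | 7.0 points | 16.7% | 30.1% |

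The 150 column applies only if the whole enrolment target of 300 were analysed. The false-positive rate is higher there than at 70, so a larger trial does not cure the problem.

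**Check of the proposed denominators on the same scenario.** With all randomised patients as denominator, both arms have 20 clear DCIS patients over the same number randomised, so the difference is zero. If patients with invasive carcinoma on biopsy are put back, the VAE rate returns to 20/100, equal to control; invasion that both techniques find adds equally to both arms. Selection of this kind alone therefore produces no difference in either analysis.

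**The case against.** The strongest defence is that selection on histology is unavoidable and partly intended. VAE is done in the biopsy session, so patients cannot be randomised after histology, and those with benign results have no surgical endpoint. The article seeks patients for whom avoiding surgery is safer, meaning those still called DCIS after the biopsy they had; better classification is part of that strategy. This stands as a reason to keep the DCIS comparison. It does not make that comparison one between randomised groups, nor show that a difference is due to removal. The planned logistic regression does not help either, because hidden invasion in control patients is unknown until surgery.

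The size may also be small. The 26% is an upper figure and not specific to small, unifocal, low/intermediate-grade lesions. That VAE finds half to all of the invasion yet removes no more lesions is a limiting case. This stands: the table is an illustration, not an estimate.

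Two stronger readings are tempting and are not supported:
- *That having surgery also depends on the arm.* It is a further condition applied after randomisation, and a dependence is possible where removal is known to be complete. The article does not document one. Study design says, without distinction by arm, that the DCIS patients will have surgery, and the Introduction puts surgery in DCIS at over 98%.
- *That the underestimation comparison is tilted towards VAE in the same way.* The smaller VAE denominator raises the VAE underestimation rate. With u = 0.26 and r = 0.5 it is 0.13/0.87 = 14.9%, against 13.0% on the full base. That distortion is modest and works against VAE, and biopsy-confirmed DCIS is the denominator the article intends.

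A condensed article may leave much to a full protocol or SAP. The point here is what it does state: the eligibility rules and the balance expectation.

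**Conclusion.** The concern holds for selection on the biopsy result and for the VAE-only haematoma exclusion. The article's expectation of even distribution conflicts with its own secondary aim, and the primary contrast as planned can favour VAE with no gain in removal. In the illustration the spurious gain is about 1 to 2 points at 10% hidden invasion and 3 to 7 points at 26%, against the planned 16. It rests on 20% control clearance, on r between 0.5 and 1, and on no true removal benefit. The true size cannot be fixed from the article. No figure is available for the haematoma exclusion, and its direction is not documented. Nothing in the verdict depends on surgery uptake differing by arm.

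**What to change.** 1. Delete the statement that DCIS patients are expected to be evenly distributed.
2. Keep patients whose haematoma stopped the second sequence in their randomised arm for analysis. This changes the analysis set only, not how the procedure is conducted.
3. Keep the DCIS comparison and add two pre-specified supportive analyses by randomised arm:
   - (a) patients with DCIS on biopsy and no pathology at surgery, divided by all randomised;
   - (b) the no-pathology rate among all randomised patients with DCIS of any grade or invasive carcinoma on biopsy.

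   State that (b) reduces but does not remove the selection, since DCIS missed by limited sampling would still be absent from control only. State that (a) keeps the randomised groups but combines detection with removal, and is diluted by benign biopsies.
4. Report missed invasive carcinoma divided by all randomised alongside the underestimation rate among biopsy-confirmed DCIS, noting that missed invasion is unobserved in patients without surgery.
5. State that a difference seen only in the selected set will not be attributed to lesion removal.

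**Cost.** Biopsy histology is already recorded (Table 1). Routine surgical pathology must additionally be retained for patients with a malignant biopsy who are now excluded; the article does not say that it is collected. The new analyses are supportive, so they add no second success criterion. The headline contrast may shrink.
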